## Abstract

**Background:**

Human papillomavirus (HPV) is the most common sexually transmitted infection worldwide and imposes a significant public health burden. In 2019, HPV was responsible for approximately 620,000 cancer cases in women, 70,000 in men, and more than 300,000 deaths globally. Despite the proven efficacy of the vaccine, vaccination rates remain alarmingly low in certain regions of France. In Réunion Island, only 16% of girls and 9% of boys under 16 years old were fully vaccinated in 2024. This underscores the need for increased awareness, education, and outreach programs. Peer learning is well-established in health education, whereas serious game–style card games are newer and require further research. Both methods have been shown to improve knowledge on specific topics.

**Objective:**

The main objective of this study is to assess the impact of 2 awareness-raising strategies on increasing HPV vaccination rates among middle school students by actively involving them in the process.

**Methods:**

This protocol describes the design of a randomized, open-label, controlled trial aimed at evaluating the effectiveness of 2 awareness-raising interventions—peer learning and a card-based serious game—in improving HPV vaccination rates among middle school students in Réunion Island. The study will span an entire school year, beginning in August. Approximately 3600 students from 24 middle schools in Réunion Island will be included, with schools randomized into 3 groups of 8 each: (1) a control group receiving the existing national vaccination campaign initiated by the French public health institute; (2) ambassador classes, whose students will receive education about the HPV vaccine and later educate other students in the same school; and (3) serious game card group, where students can play and learn about HPV during a science class. The primary outcome will be the proportion of teenagers who initiate the vaccination process, compared across the 3 groups using appropriate statistical methods. Anonymized data will be collected at the end of the school year using social security records. Teenagers’ knowledge of HPV will be assessed both before and 3 months after each intervention, and satisfaction will also be evaluated after the intervention in each group.

**Results:**

As of May 2025, a preliminary result enrolling 124 students showed an increase in vaccination coverage after students played a serious game. We expect higher vaccination rates in the intervention groups compared with the control group, although it is difficult to predict which strategy will be more effective. The estimated target vaccination coverage for groups b and c is 45%.

**Conclusions:**

This study aims to improve HPV vaccination rates among teenagers in Réunion Island by evaluating the impact of 2 awareness-raising strategies using innovative and engaging tools. If successful, this approach could be adapted and implemented in other regions of France or internationally.

**International Registered Report Identifier (IRRID):**

PRR1-10.2196/73366

## Introduction

Human papillomavirus (HPV) is a widespread sexually transmitted infection that affects more than 1 in 5 people globally [1]. It is estimated that about 80% of men and women will be exposed to HPV at some point in their lives. With a global prevalence of 31% in men and 32.1% in women [2,3], HPV represents a major public health concern due to its established role in the development of multiple cancers [4], most notably cervical cancer, which remains the fourth most frequent cancer in women worldwide. The World Health Organization reported 660,000 new cervical cancer cases and 350,000 related deaths in 2022. In France, HPV is responsible for over 6400 cancers annually, including cervical, vulvar, vaginal, penile, anal, and oropharyngeal cancers. On Réunion Island, cervical cancer is the third most common cancer in women.

Prevention of cervical cancer is mainly based on screening with Papanicolaou (Pap) smear tests and HPV vaccination. Despite the proven safety and effectiveness of HPV vaccines in reducing the incidence of precancerous lesions and genital warts [5-7], vaccination coverage in France remains insufficient. As of 2023, only 45% of girls and 16% of boys aged 16 were vaccinated [8]. In Réunion Island, coverage is even lower: in 2022, only 12.7% of adolescents under 16 had received at least one dose of the HPV vaccine. Following the national vaccination campaign launched in 2023, only 6.8% of seventh-grade students were vaccinated at school in Réunion. Taking into account children vaccinated outside school by their general practitioner, the rate modestly increased to 27% for girls and 16% for boys. Nevertheless, these figures remain far from the thresholds needed to achieve herd immunity and effective cancer prevention [9].

The low uptake in Réunion Island may be attributed to a lack of information, fear of adverse events, and limited engagement from both health care professionals and families [10,11]. In countries such as Australia, Belgium, Portugal, and the United Kingdom, school-based HPV vaccination programs have achieved coverage rates exceeding 80% [12]. These programs reduce access barriers, promote equity, and provide opportunities for engaging educational interventions.

Educational strategies themselves are key determinants of success. Traditional top-down health messages may be poorly received by adolescents, particularly when sensitive topics such as sexually transmitted infections are involved. In response, 2 innovative, youth-centered approaches have emerged: peer-led education (ambassador programs) and serious games.

Peer education leverages the credibility, relatability, and social dynamics of adolescence. Studies have shown that adolescents are more likely to engage with and retain information delivered by peers than by adults or authority figures. In a 2018 study conducted in Niger with more than 1000 students, peer-led HPV education significantly increased knowledge scores (from mean 12.94, SD 9.23 to mean 53.74, SD 10.69, *P*<.001) [13]. This underscores the power of peer-to-peer communication in culturally and resource-diverse settings.

In the field of health sciences, peer-assisted learning has been widely applied in clinical education. A systematic review by Markowski et al [14], analyzing 47 articles from 8 countries, concluded that peer-assisted learning improves skills, reduces stress, and increases confidence among students [14]. Importantly, these effects are not limited to the “ambassadors”—students receiving information from their peers also benefit significantly from the learning process [15].

In the context of vaccination, peer influence has been shown to enhance acceptance, particularly when combined with school-based efforts and community engagement. Peer-led interventions not only promote knowledge but also shape attitudes and behavioral intentions—factors especially relevant to HPV vaccination, which is often stigmatized or misunderstood.

Serious games—defined as games designed for a primary purpose other than pure entertainment—are increasingly used in health education. They offer immersive, interactive learning experiences that promote engagement, critical thinking, and long-term retention of knowledge. In recent years, serious games have been applied to topics ranging from antimicrobial resistance to smoking prevention.

Already in 2016, it was highlighted that serious games, through their unique combination of pedagogy and play, foster active learning, strengthen motivation, and adapt to different learner profiles. While recognizing the need for thoughtful integration into the pedagogical framework, the literature also provides tools for selecting and using these games appropriately [16].

In the French Antilles, unpublished pilot projects used serious games to address tobacco and alcohol prevention in adolescents. In mainland France, the Paris Committee and the French League Against Cancer developed a serious card game to educate students about the harms of smoking. A 2019 literature review of serious games in health education found that, while most studies focused on participant satisfaction, several also reported improvements in knowledge, decision-making, and self-efficacy [17].

A Swiss study conducted in 2020 reported behavior change following increased knowledge of COVID-19 protection measures in a small sample of employees in a long-term care unit [18].

A 2021 Irish study evaluated the impact of a serious game on influenza vaccination among nursing students. Postintervention, knowledge scores rose from 68% to 85%, and positive attitudes toward vaccination improved significantly [19]. Although data on serious games for HPV remain limited, these early findings support their potential as engaging tools for behavior change, particularly when integrated into school curricula.

Building on the findings of Tran et al [20], we hypothesize that both peer education and serious games can improve HPV vaccination uptake among adolescents. To evaluate this, we have designed a randomized controlled trial comparing 3 strategies in middle schools across Réunion Island (Textbox 1).

Strategies in middle schools across Réunion Island.1. Control groupStandard school-based vaccination campaign with no additional educational component.2. Ambassador groupImplementation of a peer-led education model, with trained student ambassadors delivering information to their peers.3. Serious game groupDelivery of a custom-designed, human papillomavirus–focused serious game to promote learning and engagement.As the local education authority of Réunion Island does not permit promotion of this type of intervention in virtual form, to limit screen exposure among young people, we have planned the game in a card-based format.

Comparing peer-led (ambassador) education and serious games within the same trial will allow us to determine the most effective and scalable strategy for improving HPV vaccination uptake in Réunion Island. While both approaches have shown promise in preliminary studies and international contexts, they differ in required resources, modes of engagement, and potential for long-term implementation. Peer-led education depends on sustained student involvement and social interaction, whereas serious games provide a more immersive, standardized, and potentially reproducible experience. By rigorously evaluating their respective impacts in a controlled setting, this study will inform future public health programming. Once the most effective and cost-efficient strategy is identified, efforts and resources can be directed toward its wider deployment at the regional level—and potentially beyond—to maximize public health impact and reduce HPV-related disease burden among adolescents.

By targeting students in schools—where barriers to access can be minimized—we aim to advance the long-term goal of reducing the HPV-related disease burden in underserved regions such as Réunion Island.

## Methods

### Trial Design

This is a randomized, controlled, open-label intervention study based on 2 awareness strategies for HPV vaccination in Réunion Island. A prototype of the serious game was created in May 2025, and the service company will devote several weeks to producing the final materials. The card game is expected to be ready for the start of the school year.

Colleges (selected from lists provided by the local education authority in March-April) will then be randomly assigned to 3 groups, with 8 colleges per arm:

Reference arm: no intervention; schools will only follow the government’s vaccination campaign.Ambassador arm: implementation of specific HPV vaccine education to create an ambassador class.Serious game arm: distribution of the card-based serious game.

The unit of randomization will be the middle school. Each school will be assigned to 1 of the 3 intervention arms (1, 2, or 3) according to a randomization list. The allocation ratio will be 1:1:1, with stratification by middle school level. To minimize imbalance between schools, a constrained randomization plan will be used (PROC PLAN; SAS Institute Inc). The randomization list will be generated by a statistician at the Methodology and Data Management Center before the start of the study. A document describing the randomization procedure will be kept confidential within the same center.

The directors of the randomized schools will be invited to participate in the study. Our study is supported by the rectorship of Réunion Island, which has already written to all directors to request their assistance with this project.

Once school directors agree, they will be asked to identify 1 or 2 teachers, on a voluntary basis, to help implement the study in each school. From our experience, teachers are highly motivated to take part in public health initiatives, particularly those involving playful learning.

If directors decline participation, a new randomization will be conducted in additional schools to ensure school buy-in.

Interventions will be conducted only in seventh-grade classes, targeting children around 12 years of age.

All participants will complete an HPV baseline knowledge questionnaire before the intervention and again up to 3 months afterward.

Following the trial, the team will collect data on vaccination uptake, with initiation of the vaccination schedule (at least one dose) considered sufficient for assessment, as the World Health Organization has concluded that a single-dose HPV vaccine may provide solid protection [21].

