**Figure 1 figure1:**
[figure not shown]
Participants timeline 
T0 : pre-intervention questionnaire
T1 : post intervention questionnaire at 3 months
T2 : only for ambassador classes : information by ambassador classes to their peers in 7th grade class
T3 : collection of vaccination status.

In August, at the beginning of the new academic school year, parental consent will be collected.

In September, children will be enrolled after confirming that their parents do not object to participation.

Vaccination campaigns typically occur in December and June, with the first dose usually given in December and the second dose in June, although vaccination can also be initiated with the first dose in June, all scheduled before school holidays.

Between September and December, the following events will occur:

In the ambassador group, a facilitator, after receiving prior training, will introduce HPV to students in the ambassador classes using a standardized slideshow identical across all classes. These students will then be responsible for conveying this information to other seventh-grade classes in their school. They will have the autonomy to choose the format for delivering the information to their peers (eg, games, presentations, films, posters, slideshows, comics).In the serious game group, 1 facilitator will explain the functioning and rules of the game to volunteer science teachers. The game is designed so that teachers can work independently with the students. Teachers may choose when to conduct the serious game during school classes before the vaccination campaigns.

At the end of the school year, around July, vaccination status will be collected using the French social security system, following anonymization of social security numbers.

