### Patient and Public Involvement

Following the distribution of information leaflets to parents and students, and after obtaining consent from school directors, the schools will be randomized. The research team, together with teachers, will verify any potential objections and ensure that students whose parents object do not participate in the interventions. Parents may withdraw their child from the study at any time by simple request. Participants will have the right to receive information about the study, including the results.

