### Recruitment

Our sample will include seventh-grade middle school students from randomly selected schools in Réunion Island, following approval from the school directors. These schools will be randomly assigned to 1 of the 3 groups in a 1:1:1 ratio using a randomization algorithm. All students attending the selected schools will be invited to participate in the study (Figure 2).

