### Eligibility Criteria

Inclusion criteria are students in seventh-grade classes from middle schools in Réunion Island who are randomly selected and assigned to the study.

Exclusion criteria are students with parental opposition to participating.

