#### Blinding

Given the nature of the interventions, blinding will not be implemented in this study. No participants will be blinded during the trial.

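### Trial Design assigns schools to arms before directors agree and replaces those who decline, while two other sections put agreement first; the Trial Design order permits selection after allocation

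*Protocol article*

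**What the plan says.** **Order in Trial Design.** Schools come from the education authority's lists: "Colleges (selected from lists provided by the local education authority in March-April) will then be randomly assigned to 3 groups". After describing the stratified, constrained allocation, the section continues: "The directors of the randomized schools will be invited to participate in the study". For refusals it provides: "If directors decline participation, a new randomization will be conducted in additional schools to ensure school buy-in".

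**Order elsewhere.** Patient and Public Involvement says that "after obtaining consent from school directors, the schools will be randomized". Recruitment agrees: "Our sample will include seventh-grade middle school students from randomly selected schools in Réunion Island, following approval from the school directors", with assignment to the three groups described in the sentence after that.

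**Families.** Settings states: "In August, at the beginning of the new academic school year, parental consent will be collected". Eligibility Criteria then removes students: "Exclusion criteria are students with parental opposition to participating". The ethics section has information leaflets going to parents in June and August.

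**Masking.** "Given the nature of the interventions, blinding will not be implemented in this study". Study Limitations adds only that students and teachers in control schools may be told of a general campaign, without details of the strategies tested elsewhere.

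**Analysis.** Statistical Analysis promises intention-to-treat by randomized group. Study Limitations specifies a mixed logistic model with a random intercept for school.

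**The concern.** The article gives two incompatible sequences for the step on which the randomized comparison rests. The choice matters because the arms make different demands:

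- The control arm adds questionnaires to the usual campaign.
- The ambassador arm needs a facilitator-led session and then peer sessions in the other seventh-grade classes.
- The game arm needs a one-hour teacher-run session in every seventh-grade class.

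A director who knows the arm may weigh those demands, or the school's attitude to vaccination, before answering. If decliners are then replaced, the schools analysed in an arm are no longer simply those that chance put there. The same can happen with families if they know the arm when they decide whether to object.

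An endpoint taken from social security records protects against biased measurement. It does not protect against selective entry.

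**Working it through.** The main check is textual. The arithmetic only gives a scale, because the documents state no refusal or objection rates and so offer no figure to reproduce.

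**1. The two sequences**

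- Trial Design: list of schools, assignment to arm, invitation to directors, and a new randomization in further schools if any decline.
- Patient and Public Involvement: leaflets, directors' consent, randomization, then a check for parental objections.
- Recruitment: random selection, directors' approval, assignment to arm.

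The second and third agree with each other and conflict with the first. Could the phrase about randomized schools in Trial Design mean only schools drawn at random from the list? That is possible but strained. Assignment to arms has just been described, and a refusal leads to a further randomization.

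**2. Can refusal depend on the arm?** Under the Trial Design order, the allocation exists when directors answer. The trial is open-label, the demands differ by arm, and no section says the arm is withheld until the answer is given. Arm-dependent refusal is therefore possible, but the text does not establish that it will occur.

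**3. Would the model remove it?** The random intercept allows for variation between schools. If the schools retained in one arm have a different average underlying coverage, that difference is absorbed into the fixed effect for the arm. The model handles clustering, not selection.

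**4. Scale at school level.** Inputs from Sample Size: control coverage 30%, intervention coverage 45%, intracluster correlation 0.1, 8 schools per arm. The planned difference is 45 − 30 = 15 points.

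Between-school SD = √(ICC × p × (1 − p)) = √(0.1 × 0.30 × 0.70) = √0.021 = 0.145, or about 14.5 points.

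Shift in an arm = (schools replaced ÷ 8) × (coverage of replacements minus coverage of decliners).

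Assumed range: 1 to 4 schools replaced, and a gap of 0.5 to 1.5 SD.

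- Smallest: (1 ÷ 8) × 0.5 × 14.5 = 0.9 points.
- Middle: (2 ÷ 8) × 1.0 × 14.5 = 3.6 points.
- Largest: (4 ÷ 8) × 1.5 × 14.5 = 10.9 points.

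Milder assumptions, with 10% to 30% of schools replaced and a gap of 5 to 10 points, give 0.1 × 5 = 0.5 to 0.3 × 10 = 3 points. If the gap is zero, so is the expected shift. If it is negative, the sign reverses.

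A simulation with no true effect gives intermediate values. It drew schools with mean coverage 30% and ICC 0.1, let refusal occur in the intervention arm only, and replaced decliners until the arm had 8 schools. Refusal at an average school was set at 10% to 40%, and the log odds of refusal fell by 0.5 to 1 per SD of coverage. The mean spurious difference was 0.7 to 5.0 points. With refusal unrelated to coverage it stayed within 0.15 points of zero, which is simulation noise.

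**5. Scale at family level.** Suppose an extra share *o* of families objects in one arm only and none of their children would have been vaccinated. True coverage of 30% then appears as 0.30 ÷ (1 − *o*):

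- *o* = 5%: 0.30 ÷ 0.95 = 31.6%
- *o* = 10%: 0.30 ÷ 0.90 = 33.3%
- *o* = 20%: 0.30 ÷ 0.80 = 37.5%

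This is an extreme case. If objectors' children would have been vaccinated at the same 30%, nothing changes.

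**The case against.** The strongest reply is that the sound order already appears twice, so Trial Design may simply be loosely worded and one section needs aligning with two others. That is fair, and it makes the repair easy. It does not make the contradiction harmless, because the replacement rule appears only in the section with the unsafe order.

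Replacing a school whose director declines before the draw does no damage and helps reach 24 schools. This stands: the timing of the rule is at fault, not replacement as such.

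Four stronger readings are tempting but unsupported:

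- **A replacement drops into the vacated arm, so the stratification and constraint are lost.** The article says only that a new randomization takes place, not how replacements are allocated.
- **Directors or parents know their arm when they decide.** No section says so. Patient and Public Involvement has the leaflets going out before randomization, and nothing says that they differ by arm.
- **The bias must favour the interventions.** This is plausible if the most reluctant schools decline, but the documents do not show it.
- **Replacement contradicts the intention-to-treat text.** Statistical Analysis lists a college's nonparticipation in its allocated intervention as a deviation. That can mean an enrolled school that does not deliver its intervention, which is a different event from a director declining at the outset. The two rules can coexist.

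**Conclusion.** The contradiction over the order of agreement and allocation is certain on the text. The bias is conditional. It requires that the Trial Design order is followed, that refusal depends on the arm, and that decliners and replacements differ in underlying coverage. Its size and direction are unknown. The 0.9 to 10.9 points show what the protocol's own ICC would allow under assumed replacement numbers and gaps; they do not estimate what will happen. At the upper end the shift would be a large part of the planned 15 points.

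At family level the concern is weaker. Objection excludes students in every arm, so only a difference between arms matters, and the documents do not say whether families know the arm. The 31.6% to 37.5% figures are illustrations only.

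The order should be settled before allocation, because selective entry cannot be reliably undone in the analysis.

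**What to change.** Align Trial Design with Patient and Public Involvement and Recruitment:

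1. Obtain each director's agreement to accept any of the three arms.
2. Replace schools that decline only at this stage, before the draw.
3. Randomize the 24 agreeing schools once, with the planned stratification and constraint.
4. Allow no replacement after allocation. A school that later withdraws stays in its assigned arm for the intention-to-treat analysis, where vaccination records can be obtained.
5. Use the same arm-neutral parent leaflet in all arms and, where feasible, record objections before the arm is disclosed.

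The cost is a change of wording and moving contact with directors ahead of the draw; the rectorship has already written to all of them. Some directors may hesitate to agree before knowing their arm. Holding back the arm until objections are recorded in August leaves little time before activities begin in September, so that step may not be workable everywhere. The number of schools does not change.
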